### Health behavior

Changes in health behaviors is investigated from baseline to post assessments.

#### Physical activity

Physical activity is assessed with a shortened German version of the International Physical Activity Questionnaire (IPAQ, [67]) including four items, two for vigorous and two for moderate activities. As an example for vigorous intensity, following the stem “During the last seven days, on how many days did you do vigorous physical activities like heavy lifting, digging, aerobics or fast bicycling?” participants indicate vigorous physical activity frequency in days per week. Additionally, it is asked “How much time did you usually spend doing vigorous physical activities on one of those days? With participants indicating minutes of vigorous intensity per day. The IPAQ has proven to be a reliable and valid instrument in young and middle aged adults (36.8 ± 7.9 years; Spearman’s rank correlation coefficient clusters around 0.8, [68]).

#### Nutrition

Nutritional behavior is assessed through a Food Frequency List, adapted and proven to be valid, according to Winkler and Döring [69].The food frequency list entails 27 food items (e.g., fish, cake, fast-food) for which participants are asked to indicate on a six-point Likert scale ranging from 1 (almost daily), 2 (multiple times per week), 3 (once per week), 4 (multiple times per month), 5 (once per month) to 6 (never) how frequently they consume each item respectively. Spearman’s rank correlation coefficients range between 0.15 (sweets and candies) and 0.60 (curds, yoghurt, sour milk, milk, butter milk, mineral water.

#### Mindfulness

Mindfulness is assessed with a short and psychometrically sound version of the Freiburger Mindfulness Inventory [70, 71]. Participants are asked to rate each of the 14 items (e.g.,”I am open to the experience of the present moment”) while taking into account the last four weeks (α = 0.89). Responses are given on four-point-Likert scale ranging from 1 (rarely), 2 (occasionally), 3 (fairly often) to 4 (almost always). The mean value of all items is calculated to build the scale.

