### Objectives

The present study outlines the protocol for a longitudinal, multicenter single-arm study among health care professionals investigating the role of theory-based motivational and volitional predictors for healthy habit formation in daily life based on a mHealth intervention targeting physical activity, healthy nutrition and mindfulness behaviors (i.e., engaging in mindfulness techniques and relaxation exercises). The aim of this paper is to outline the study protocol including a detailed description of the mHealth intervention, the evaluation plan, and the study design. The main purpose of this trial is to understand the habit formation process for physical activity, nutrition and mindfulness behaviors and its predictors. As preliminary hypothesis (hypothesis 1 a-e), we expect to find positive changes from baseline to post assessments (i.e., 100 days post baseline) in: a) habit strength, b) motivational constructs (i.e., intention, outcome expectancies, self-efficacy), c) volitional constructs (i.e., action planning), d) health behavior (i.e., physical activity, nutrition, mindfulness behaviors) and e) health status (i.e., stress, back pain, well-being, physical and psychological health, body mass index). For the primary endpoint (habit strength over time) and to understand predictors of habit formation over time, we hypothesize that a) habit strength at post-assessment is predicted by baseline motivational and volitional constructs, controlling for baseline habit strength (hypothesis 2), b) that health behavior and c) health status at post assessment are predicted by motivational and volitional constructs as well as habit strength at baseline (hypotheses 3 and 4, respectively). Finally, we hypothesize that next-week habit strength will show positive associations with behavior-related motivational (5a) and volitional constructs over time (5b).

Additionally, we conduct a process evaluation by evaluating participants’ experiences and satisfaction with the app. For the process evaluation a mixed-methods approach will be applied involving questionnaires and structured interviews. The items addressed in this protocol paper are based on the 2013 Standard Protocol Items: Recommendations for Interventional Trials (SPIRIT) statement [[58]; see Additional file 1].

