##### Intention

Intention is assessed with two items in accordance with Schwarzer, Schütz, Ziegelmann, Lippke, Luszczynska and Scholz ([63]; e.g., I intend to engage in at least 30 min physical activity with at least moderate intensity (i.e., mildly sweating) in the next four weeks on a nearly daily basis; I intend to eat at least five portions of fruit and vegetables daily in the next four weeks; I intend to practice mindfulness activities at least three times per week in the next four weeks, α = 0.56—0.79).

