##### Self-efficacy

Self-efficacy is assessed with five items in accordance with Schwarzer and Renner [64]. Following the stem “I am sure I can engage in at least 30 min of physical activity with at least moderate intensity on an almost daily basis/I am sure I can eat at least five portions of fruit and vegetables/ I am sure I can practice mindfulness activities for ten minutes at least three times per week … in the next four weeks, even if,…” participants indicate how likely it is to engage in the respective behavior even if they are for example “tired” (α = 0.87—0.88).

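### Mindfulness behaviour is defined as practising techniques but measured at baseline and post by an inventory of mindful experience, so hypotheses 1d and 3 test a different construct in this domain

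*Protocol article*

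**What the plan says.** The Objectives describe the third target as "mindfulness behaviors (i.e., engaging in mindfulness techniques and relaxation exercises"), that is, as something a participant does. Hypothesis 1 expects positive change from baseline to post in "d) health behavior (i.e., physical activity, nutrition, mindfulness behaviors"). Hypothesis 3 states that health behaviour "at post assessment are predicted by motivational and volitional constructs as well as habit strength at baseline".

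The *Health behavior* section fixes the timing: "Changes in health behaviors is investigated from baseline to post assessments". Under its *Mindfulness* heading, the measure is given as follows: "Mindfulness is assessed with a short and psychometrically sound version of the Freiburger Mindfulness Inventory". It has 14 items, rated from 1 (rarely) to 4 (almost always) with reference to the last four weeks, and the score is the item mean. The one item shown is "I am open to the experience of the present moment".

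The mindfulness predictors ask about practice. Intention reads "I intend to practice mindfulness activities at least three times per week in the next four weeks"; self-efficacy reads "I am sure I can practice mindfulness activities for ten minutes at least three times per week". The outcome expectancy, action planning and automaticity items for this domain are likewise about carrying out mindfulness activities.

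**The concern.** The definition and the predictors concern an activity, while the outcome concerns a quality of experience. The two can come apart: someone may start practising regularly and score the same on the inventory, or score higher without practising anything.

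For hypothesis 1d, a rise in the inventory mean would be reported as a change in mindfulness behaviour although practice was not the thing scored. For hypothesis 3, a null result would be ambiguous, because the predictors may not predict practice, or practice may not move the inventory. A positive result would be reported as predicting a behaviour that the outcome does not record.

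**Working it through.** The protocol gives no figure to reproduce. The check is whether definition, hypotheses, outcome, predictors and timing refer to the same thing.

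**1. Outcome against definition, by domain** (*Health behavior* and its subsections)

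| Domain | Baseline and post measure | What is scored |
|---|---|---|
| Physical activity | Four items from a shortened IPAQ | Days per week and minutes per day of activity |
| Nutrition | Food frequency list, 27 foods | How often each food is eaten |
| Mindfulness | 14-item inventory, mean score | Self-rated experience, judged from the example item and scale |

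In the first two domains the score counts the behaviour. In the third, nothing described refers to sessions, days or minutes of practice.

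**2. Predictors against outcome.** *Statistical analysis* plans hierarchical linear regressions of post-assessment health behaviour on baseline motivational, volitional and habit-related predictors. For mindfulness, every construct described under *Psychosocial determinants* (intention, outcome expectancies, self-efficacy, action planning, automaticity) is worded for practising. The regression for hypothesis 3 would set these against the inventory mean.

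**3. Could another measure supply practice at both time points?**

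- *Weekly self-monitoring item.* It asks on how many of the last 7 days favourite exercises were practised (0 to 7) and covers mindfulness. *Psychosocial determinants* lists self-monitoring among the weekly contents at t1 to t13, not among those of baseline (t0) or post (t14). It is limited to self-chosen favourites, and the analysis section gives it no role in 1d or 3.
- *Wizard at account creation.* Participants estimate their current mindfulness behaviour (*Description of the intervention*). The stated use is tailoring of content, and no post counterpart is described.

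**4. Count.** Measures of mindfulness practice described as an outcome at both baseline and post: 0. Measures of mindful experience at both: 1.

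**5. Reach.** The statistical power section names automaticity over time as the primary outcome, and for mindfulness its stem is worded for practice. Hypotheses 1a and 2 use habit strength at baseline and post, and hypothesis 5 uses the repeated assessments. None of them uses the inventory as its outcome.

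**The case against.** Four arguments can be made for leaving the plan alone.

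*Practice is collected, so the hypotheses are not beyond reach.* This stands in part. The last weekly assessment is at booking date + 91 and post is at + 99, 99 − 91 = 8 days later, so a late practice value exists that could inform hypothesis 3. A reader might infer that 1d and 3 cannot be answered at all for mindfulness. The documents support only that they are not answered with the measures the plan assigns to them. For 1d the weekly item does not help, since it has no value from before the app starts.

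*Only one of the 14 items is shown.* This stands. A reader might infer that the inventory contains no item on practice; the other 13 items are not in the document, so the point rests on the example item and the response scale. The assessment schedule (Fig. 3) is also not shown, so the absence of a practice item at baseline and post is judged from the text.

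*Data management commits to validated questionnaires only, so an ad hoc item would be a step back.* This is weak. The protocol already relies on single items for weekly self-monitoring, emotional state and back pain. It is nevertheless a real cost of the fix.

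*The consequence is limited.* This stands. Hypothesis 1 is called preliminary, the limitations section already says that effectiveness cannot be evaluated, and the primary endpoint is not touched.

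Two further inferences should not be drawn. One is that the mismatch makes the three domains non-comparable: they never share a metric, and no comparison across domains is planned. The other is a numerical attenuation of effects: that would need the correlation between practice and inventory score, which the document does not give, and the assumption that the inventory moves only through practice.

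**Conclusion.** The point holds as a mismatch between construct and measure in one of three domains, affecting two hypotheses (1d and 3). Followed as written, the plan would report an experience score as mindfulness behaviour. The primary endpoint, hypotheses 1a, 2 and 5, and the physical activity and nutrition domains are unaffected.

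The conclusion rests on two readings: that the example item and scale represent the inventory, and that the text describes all baseline and post outcomes for this domain. It needs no assumption about effect size, and no numerical bias is claimed. The change is worthwhile because it is cheap and alters what the trial can say about mindfulness behaviour.

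**What to change.** **If baseline collection allows:** add one item at baseline and post asking on how many of the last 7 days any mindfulness or relaxation exercise was practised. It can keep the 0 to 7 format of the weekly item but should not be limited to favourites, which do not exist at baseline. Name it as the mindfulness behaviour outcome in 1d and 3, and report the inventory separately as a psychological outcome. The cost is a slightly longer form at two assessments and reliance on an unvalidated single item.

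**If baseline collection is too advanced:** relabel the inventory as mindful experience and reword 1d and 3 for this domain accordingly. This costs only text, but gives up the claim about behaviour. The weekly practice-days value at booking date + 91 may be added as a supportive outcome for hypothesis 3 only, with its restriction to favourites stated.

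**Not recommended:** comparing the first with the last weekly value for 1d. The first value falls after the app has started, and participants choose favourites over the first couple of weeks, so a low early count may partly mean that none had been chosen. A rise could then be an artefact in the direction of the hypothesis.

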### Health status

Changes in health status are examined from baseline to post assessments and mean values will be calculated to build each scale.

#### Perceived stress

Perceived stress is assessed with the Perceived Stress Scale (PSS-4 [72],), a short instrument assessing the degree to which situations in a person’s life over the past month are appraised as stressful. Participants are asked to rate their feelings and thoughts (e.g., “In the last month, how often have you felt that you were unable to control the important things in your life?”) during the last months (α = 0.80—86). Responses are given on a five-point-scale range from 0 (never) to 4 (very often). The PSS-4 has been shown acceptable psychometric properties [73].

#### Back pain

Back pain is assessed with two single items. Participants are asked to rate their back health with response options ranging from 1 (bad), 2 (not good), 3 (satisfactory), 4 (good) to 5 (very good) and to indicate if they suffered from back pain within the last three months (response options: yes – no).

#### Mental well-being

Mental well-being is assessed with the World Health Organization—Five Well-Being Index (WHO-5), a short self-reported measure of current mental wellbeing. For the German version, excellent psychometric properties have been reported [74]. The WHO-5 includes five statements, which participants rate in relation to the past two weeks and according to the following scale: 0 (at no time), 1 (some of the time), 2 (less than haft of the time), 3 (more than half of the time), 4 (most of the time) and 5 (all of the time). The total raw score, ranging from 0 to 25, is multiplied by the factor four to give the final score, with 0 representing the worst imaginable well-being and 100 representing best imaginable well-being. Internal consistency has been shown to be very good (Cronbachs` α = 0.92).

#### Physical and mental health status

Physical and mental health status are each assessed with one single item. Participants are asked to rate their general physical and their general mental health status with response options ranging from 1 (very bad), 2 (bad), 3 (moderate), 4 (good) to 5 (very good).

### Stable variables

Stable variables will be assessed at baseline only. Mean values will be calculated.

#### Self-control

Trait self-control is assessed at baseline by means of the brief, German version of the Self-Control Scale (SCS-K-D [75, 76],) containing 13 items (e.g., “I am good at resisting temptation”), which participants rate according to the following scale: 1 (not at all true) to 5 (totally true). The brief version has shown to be reliable and valid ([75]; α =  ≥ 0.93).

#### Organizational health climate

Exercise, eating and mindfulness climate are assessed by the validated Organizational Health Behavior Climate scale (OHBC, [77]) using the organizational practices subscale only (i.e., 4 items per behavioral domain). Given that the OHBC features exercise and nutrition behaviors only, respective items for mindfulness behaviors were added. Participants rate their organizational exercise, nutrition and mindfulness practices (e.g., “In this organization, there are posters featuring exercise and physical activity/brochures and information on the Internet about healthy nutrition/posters with mindfulness practices”) according to the following scale 1 (I do not agree at all) to 5 (I fully agree). Internal consistency has been reported for exercise and eating behaviors, respectively (α = 0.82 – 0.89).

### Process evaluation

Participants satisfaction and experiences with the app will be evaluated using a mixed-methods approach (i.e., questionnaire and structured interview). Questionnaire items assess the whole set of psychosocial items (i.e., motivational, volitional and habit formation process-related items with regard to app use) at interim assessments at week four and eight (booking date + 28 and + 56, respectively), only, and not at baseline, given that participants are not familiar with the app at study start (t0). Items derive from the respective instruments described above and participants indicate their responses on a six-point Likert scale ranging from 1 (not at all true), 2 (not true), 3 (rather untrue), 4 (rather true), 5 (true) to 6 (absolutely true), if not otherwise specified. Mean values are calculated for each scale.

#### Intention

Intention is assessed with two items (e.g., I intend to use the app at least daily in the next four weeks).

#### Positive and negative outcome expectancies

Outcome expectancies are assessed with six items (i.e., three positive and three negative). Following the stem “If I use the app at least once daily in the next four weeks…” participants indicate in how far they expect “to do something good for their health” (positive outcome expectancy) or “to have an additional obligation” (negative outcome expectancy).

#### Self-efficacy

Self-efficacy is assessed with five items. Following the stem “I am sure I can use the app at least once daily in the next four weeks, even if, …” participants indicate how likely it is to use the app even they are for example “tired”.

#### Action planning

Action planning is assessed with two items. Following the stem “For the next four weeks I have concretely planned, …” participants indicate for example “where”, “when” and “how often” they use the app.

#### Automaticity

Automaticity is assessed with two items by mans of the Self Report Habit Index. Following the stem “Using the app once daily is something …” participants indicate on a five-point Likert scale ranging from 1 (do not agree) to 5 (totally agree) if they engage in the behaviors for example “automatically”.

#### Grading

Participants are asked to rate the app using the following scale (equivalent to the German grading system, “How would you grade the app”): 1 (very good), 2 (good), 3 (satisfactory), 4 (sufficient), 5 (inadequate) to 6 (insufficient).

#### Recommendation to friends

Participants are asked to indicate on a single item whether they would recommend the app to friends and colleagues (e.g., “Would you recommend the app to friends, acquaintances and colleagues that work in the same field) with responses ranging from 1 (no), 2 (rather no), 3 (neither…nor), 4 (rather yes) to 5 (yes).

#### Semi-structured interview

Upon completion of the post-assessment (100-days post baseline) participants are invited to voluntarily take part in an interview (approximate duration 30–60 min). Main topics of the interview are: experiences with app in general, experiences with operability of app (e.g., setup), experiences with practicability (e.g., in the work context), app user behavior, opinion about personal relevance and effects of the app on health behavior. Reasons for dropout will be evaluated for participants who withdrew during the intervention period. An overview of the main interview questions is presented in Table 2.

**Table 2 Tab2:** Overview of semi-structured interview questions about participants’ experiences with the Habit Coach app (process evaluation)

Topic	Question
General experiences with app	What are your experiences with the app? Please elaborate.
Experiences with operability of app (e.g., setup)	How do you perceive the operability (e.g., setup of menu) and features of the app?
Experiences with practicability (e.g., work context)	How practicable do you perceive the app during your working routine?
App user behavior	How, how often, when and where do you preferably use the app?
Opinion about personal relevance	As how personally important and relevant do you perceive the app?
Effects of app on health behavior	What effect does the app have on your health behavior? Have you made any changes in your behaviors due to using the app? Please also think about any spontaneous negative events or unintended effects of the app. Please elaborate.

### Data management

All data are assessed through the mobile app, which will be extracted upon intervention completion in Excel files, before they are transferred in SPSS. All data collected during the various assessment waves will be stored in separate SPSS files, one file per assessment point. After data collection completion, data will be transformed in one SPSS file based on the participants’ identification numbers. Variable labels will be defined in SPSS. Additionally, information about the variables assessed is gathered in an excel codebook including variable names, labels, codes, specific item information etc. To prevent drop out, user will be contacted through reminder emails. Moreover, incomplete assessments and tasks will continuously be displayed on the home screen (i.e., “open tasks” feature). To ensure that instruments used are reliable and valid, only validated questionnaires will be utilized. To overcome data loss, all data will be stored on the servers of the Aeroscan company, which are hosted by the Domain Factory in Germany (domainfactory GmbH, [name]). The Domain Factory ensures reliability and unauthorized access to the servers. All data will be separately and confidentially stored at two different data bank systems and in line with the German data protection ordinance, ensuring a strict separation between the user’s identity (i.e., contact data) and psychosocial and demographic data. Only a few specifically trained Aeroscan IT experts can access the data. The few people with data access signed a confidentiality agreement. As long as the data are not effectively anonymized, no data usage will be conducted by the Aeroscan company, the company health care insurance or else. Only the research team (i.e., two professors, one post-doctoral researcher, one student assistant) has access to the data until anonymization. Upon termination of the study, all user data will be deleted.

Participants will be informed on every aspect of the study that concerns their participation (e.g., data collection, storage, anonymization, access to data, participant rights etc.) and have to give written informed consent to enter the program (i.e., without informed consent, access to the app is denied). With respect to data sharing activities and distribution of study results, participants are informed that data are always shared on group level means and never as individual results (e.g., in (inter-)national peer-reviewed publication, conference abstracts) and that interview data will always be pseudonymized. Lastly, the data collection will be monitored and guided by the Aeroscan company in close collaboration with the researchers. Given that this study does not involve patients, no data trial steering or data monitoring committee was assigned.

For the semi- structured interviews a coding list will be used that links participants’ names with respective interview data. Only the research team has access to this list, which will be stored, separately from the interview data, in a looked cupboard in the university. Upon interview transcription, the coding list will be deleted and the interviews will be anonymized.

